## Abstract

**Introduction:** The efficacy of conventional treatments for treating postherpetic neuralgia (PHN) remains unsatisfactory. Thus, this multicentre, randomized controlled, assessor-blinded trial aims to investigate the efficacy and safety of electroacupuncture (EA) therapy in patients with PHN.

**Methods and Analysis:** This multicentre randomized controlled trial will enroll 132 patients with PHN from 3 hospitals. All patients will be randomly assigned to either the EA combined with medication group or medication group through a computerized central randomization system in a 1:1 ratio. Outcome measures will be assessed before intervention, at 2, 4, 6 weeks after intervention and at the end of 8-week follow-up. Primary outcomes will be sensory thresholds and pain intensity. Secondary outcomes will include dosage of analgetic, quality of life, anxiety, and depression severity and sleep quality. All adverse effects will be assessed during the trial.

**Conclusions:** This study will provide evidence to ascertain whether EA is effective and safe for treating PHN.

**Ethics and Dissemination:** Ethics approval (No.ZSLL-KY-2017-025) has been obtained from the Ethics Committee of The Third Affiliated Hospital of Zhejiang Chinese Medical University. Informed consent will be signed prior to subject enrolment. The results will be submitted to international peer-reviewed journals and presented at international conferences.

**Trial Registration Number:** The study protocol has been registered in the clinicaltrials registry with the identification code NCT04594226.

## Introduction

Postherpetic neuralgia (PHN) is the most common sequela of herpes zoster (HZ) (1). It is generally defined as pain in the skin lesion area lasting for more than 1 month after the healing of HZ rash (2). PHN is characterized by persistent or intermittent pain (3), which can be spontaneous or induced. And it is often accompanied by local paresthesia, anxiety, sleep disorders, and other symptoms, which seriously affect the quality of life in patients.

Although multiple kinds of therapies have been adopted to treat PHN, the efficacy of conventional therapies (e.g., medication, local anesthesia, surgical operations) remains unsatisfactory because many of these therapies can cause side effects leading to patient intolerance (4). In addition, many of these therapies are not applicable to all patients with PHN and some patients have high-risk for recurrence. Therefore, PHN has been a worldwide health challenge and many clinicians and patients are seeking for help from complementary and alternative medicine.

As one of the most widely used complementary therapies for treating a large spectrum of diseases for thousands of years, acupuncture has advantages of simple operation and less side effects, thereby is gaining increasing popularity in the world (5). A great number of clinical trials have revealed the efficacy of acupuncture on a variety of pain conditions (6, 7), including PHN (8), but the reliability of most trials is not so robust against methodological defects, such as small sample size, absence of randomization (9).

To date, there is no high quality evidence regarding the therapeutic effect of acupuncture for treating PHN (10). Thus, this multicentre randomized controlled trial (RCT) is designed to investigate the efficacy and safety of electroacupuncture (EA) for treating PHN.

## Method and Analysis

### Study Design

This multicentre trial will adopt a randomized controlled and assessor-blinded design. Eligible participants will be randomly assigned to the EA combined with medication group or medication group in a 1:1 allocation ratio. Flow chart of the study process is shown in Figure 1 and the trial schedule of enrolment, treatments and assessments is displayed in Table 1. Participants will receive 6 weeks of treatments in two groups: EA combined with medication, medication. The reporting of this protocol is based on the Standards for Reporting Interventions in Clinical Trials of Acupuncture (STRICTA) (11) and the SPIRIT reporting guidelines (12).

**Figure 1 F1:**
[figure not shown]
Flow chart of the study process. EA, electroacupuncture; HADS, Hospital Anxiety and Depression Scale; PSQI, Pittsburgh Sleep Quality Index; QST, Quantitative Sensory Testing; SF-36, Short Form 36 Health Survey; ZBPI, Zoster Brief Pain Inventory.

**Table 1 T1:** Schedule of enrolment, treatments, and assessments.

**Study period**	**Screening**	**Baseline**	**Treatment period**	**Treatment period**	**Treatment period**	**Follow-up period**
		**week 0**	**Week 2**	**Week 4**	**Week 6**	**Week 14**
Eligibility screening	○					
Demographic data	○					
Case data	○					
Inclusion criteria	○					
Exclusion criteria	○					
Informed consent	○					
Treatment			○	○	○	
**Outcome assessment**						
(1) QST		○	○	○	○	○
(2) ZBPI		○	○	○	○	○
(3) Dosage of analgetic		○	○	○	○	○
(4) SF-36		○	○	○	○	○
(5) HADS		○	○	○	○	○
(6) PSQI		○	○	○	○	○
Safety assessment			○	○	○	○
Recurrence of PHN						○

*○, required; HADS, Hospital Anxiety and Depression Scale; PHN, postherpetic neuralgia; PSQI, Pittsburgh Sleep Quality Index; QST, Quantitative Sensory Testing; SF-36, Short Form 36 Health Survey; ZBPI, Zoster Brief Pain Inventory*.

### Participant Enrollment

Participants will be enrolled from 3 sub-centers, including the Third Affiliated Hospital of Zhejiang Chinese Medical University, Tongde Hospital of Zhejiang Province, and Lishui Hospital of Traditional Chinese Medicine. Enrollment methods will mainly include advertisements in local newspapers and health-related TV programmes, and posters in communities and hospitals. The eligibility of participants will be evaluated by the researchers based on the criteria described in details as follows.

### Inclusion and Exclusion Criteria

The inclusion and exclusion criteria are summarized in details in Table 2.

**Table 2 T2:** The inclusion criteria and exclusion criteria of PHN patients.

**Inclusion criteria**	**Exclusion criteria**
(1) Patients have a medical history of HZ; (2) Skin lesion has healed in the region of HZ, but the duration of posterior neuralgia persists for more than 30 days; (3) 20 ≤ age ≤ 80 years, male or female; (4) Participants can fully understand the study protocol and a written informed consent is signed.	(1) Acute HZ or HZ has not disappeared; (2) HZ belongs to a special type, such as ophthalmic HZ, auricular HZ, HZ that involves internal organs, meningeal HZ, and disseminated HZ; (3) Pregnant or lactating women; (4) Patients have severe complications in cardiovascular, cerebrovascular, liver, kidney, hematopoietic and other systems, or have malignant tumor, mental illness, immune deficiency, hemorrhagic disorders and other diseases; (5) Patients have severe cognitive impairment and cannot understand the study protocol; (6) Patients cannot receive EA treatment due to any reasons. (7) Patients are currently taking antithrombotic drugs.

*EA, Electro-acupuncture; HZ, Herpes Zoster; PHN, Postherpetic Neuralgia*.

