### Randomization and Allocation Concealment

All patients will be randomly assigned to either the EA combined with medication group or medication group via a computerized central randomization system. If a participant is enrolled, an independent researcher in each center, who has no contact with participants, acupuncturists and outcome assessors, will log into the computerized central randomization system to generate random sequence, dividing eligible participants into two groups in a ratio of 1:1. The researcher will make random allocation cards, each with its group allocation information and sealed into an opaque envelope, which will not be open until the first treatment.

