### Sample Size Estimation

The participants will be assigned to 2 groups in a ratio of 1:1. The sample size is calculated based on the change of ZBPI from baseline to 6 weeks after intervention, the results of which are acquired from our pilot study. It is assumed that n_1_ = n_2_, α = 0.05, and β = 0.2. Thus, each group approximately requires 57 participants. With an estimated dropout rate of 15%, a total of 132 subjects are needed, with 66 participants in each group.

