### Statistical Analysis

Statistical analysis will be performed using SPSS 17.0 for Windows (SPSS Inc., Chicago, IL, USA) by third-party statisticians. For categorical data, it will be displayed as counts and percentages. Numeric data with normal distribution will be expressed as mean ± standard deviations, whereas data with skewed distribution as median with 95% confidence intervals. Between-group differences for dichotomous variables for the baseline characteristic, such as gender and ages, will be compared according to the Chi-square test. For data in normal distribution, repeated measures analysis of variance (ANOVA) will be used to perform within-group and between-group comparison by assessing change in continuous variables before and after intervention at different time-points. For data in skewed distribution, within-group and between-group comparison will be assessed using non-parametric test. A *P* value of <0.05 will be considered statistically significant.

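### Inclusion criterion 2 does not say when its 30 days begin, while the Introduction counts the month from rash healing; the start should be stated and pain duration used as a covariate

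*Protocol article*

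**What the plan says.** The relevant statements in the protocol article are these.

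- **Introduction.** PHN is described as "pain in the skin lesion area lasting for more than 1 month after the healing of HZ rash". The month runs from healing.
- **Inclusion and Exclusion Criteria, Table 2, inclusion criterion 2.** Two conditions are joined: "Skin lesion has healed in the region of HZ", and "the duration of posterior neuralgia persists for more than 30 days". No start is given for the 30 days, and there is no upper limit on duration.
- **Table 2, exclusion criterion 1.** It removes "Acute HZ or HZ has not disappeared".
- **Elimination Criteria, item 1.** Subjects who fail the inclusion criteria but were entered by mistake are eliminated.
- **Randomization and Allocation Concealment.** A central system is used, "dividing eligible participants into two groups in a ratio of 1:1". No stratification factor is named.
- **Statistical Analysis.** For normally distributed data, "repeated measures analysis of variance (ANOVA) will be used to perform within-group and between-group comparison". No covariate is named.
- **Sample Size Estimation.** "The sample size is calculated based on the change of ZBPI from baseline to 6 weeks after intervention", with figures from a pilot study that are not reported.

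**The concern.** An entry rule has to give the same answer for the same patient at all three centres. Criterion 2 can give two. If the 30 days run from the onset of pain, a patient whose rash healed last week may enter. If they run from healing, that patient may not. The trial's stated indication is PHN, so the choice decides whether some participants have that indication as the article itself describes it.

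The ambiguity does not end at screening. Elimination criterion 1 acts on subjects who did not meet the inclusion criteria, so the two readings also differ on who is removed after randomisation. The week-14 item on recurrence of PHN in Table 1 is likewise hard to interpret for someone who did not have PHN, as described in the Introduction, at entry.

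A second matter follows. Pain of one month and pain of several years may take different courses over a 14-week study whatever the treatment. If duration predicts change in the primary outcomes, leaving it out of the model gives up precision that could be had at almost no cost.

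**Working it through.** **1. The two rules applied to one patient.** Take pain from day 0, healing on day 25 and screening on day 31, with one month taken as 30 days.

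- Table 2, clock from pain onset: the lesion has healed and pain has lasted 31 days, which exceeds 30. Eligible.
- Introduction, clock from healing: 31 − 25 = 6 days. Not yet PHN. The first qualifying day is 25 + 31 = 56, which is 56 − 31 = 25 days after this screening.
- Exclusion criterion 1 does not clearly settle it, because the lesion has healed.

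In general the two readings differ by the time from pain onset to healing.

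**2. The plan's own figure.** The article gives 57 per group, α = 0.05, β = 0.2, 15% dropout and 66 per group. No difference or SD is given, so the 57 cannot be reproduced. It can only be inverted, using a two-sided test (the article does not state sidedness):

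d = (1.960 + 0.842) × √(2/57) = 0.525.

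The dropout step gives 57 × 1.15 = 65.55, rounded up to 66, and 132 in total, as stated. The implied d serves below only as a yardstick.

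**3. What a duration covariate could gain.** If duration explains a share R² of outcome variance, the residual SD falls by the factor √(1 − R²), and

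power = Φ( d × √(57/2) / √(1 − R²) − 1.960 ), where d × √(57/2) = 2.802.

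R² is an assumption; the article gives nothing to fix it.

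| Assumed R² | 2.802/√(1 − R²) | Power |
|---|---|---|
| 0 | 2.802 | 80% |
| 5% | 2.874 | 82% |
| 10% | 2.953 | 84% |
| 20% | 3.132 | 88% |
| 30% | 3.349 | 92% |

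This takes the pilot SD as already containing the variation due to duration. If the pilot patients had all been of similar duration, pooling would instead lower the unadjusted power to 78%, 76%, 71% and 65% for the same four non-zero values of R². Nothing in the article suggests that the pilot was of that kind.

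**4. Chance imbalance.** With 66 per arm and a share p of recent cases, the difference in share between arms has SD = √(2p(1 − p)/66).

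- p = 0.5 (assumed): √(0.5/66) = 0.087. The probability of a gap of at least 10 points is 25%, and of at least 15 points 8.5%.
- p = 0.2 (assumed): SD 0.070. The same probabilities are 15% and 3%.

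If recent cases improved by 1 to 3 ZBPI points more without EA (assumed), one SD of imbalance at p = 0.5 would move the contrast by 0.087 × 1 to 0.087 × 3, or 0.09 to 0.26 points. A 15-point gap would move it by 0.15 to 0.45 points. These shifts are as likely in one direction as the other.

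**The case against.** **The criterion can be read as agreeing with the Introduction.** Healing and persistence stand in one sentence joined by a contrast, the neuralgia is called posterior, and the table is titled for PHN patients. All of this points towards pain after healing. The Introduction is also background ("It is generally defined as pain in the skin lesion area lasting for more than 1 month after the healing of HZ rash"), and Table 2 is the operative rule. This stands. The text is ambiguous, and a reader who infers that it flatly contradicts the definition, or that patients without PHN will certainly be enrolled, goes further than it allows. But background that leans one way does not supply the missing start date, and three centres must apply the rule.

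**Randomisation deals with the natural course.** A reader might infer that early recovery in recent cases biases the EA contrast. It does not: imbalance in duration has zero expectation and is carried in the standard error, so the type I error is kept. Analysing change from baseline may already absorb part of the effect of duration. This also stands, and leaves only precision.

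**Silence in an article is not a decision.** Stratification factors and covariates may appear in the full protocol or analysis plan, which are not shown. That the article names no stratification by duration is therefore not an error. Having no upper limit on duration is a choice of population consistent with the stated aim. Both parts of this stand. The covariate is a recommendation against the analysis as the article describes it, not proof of a fault.

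**The sizes are assumed.** Correct. The article contains no data on recovery by duration, and none of the figures on QST that would be needed for the other primary outcome.

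**Conclusion.** The point holds in limited form. Criterion 2 leaves the start of its 30 days open, the Introduction fixes it at healing, and on a literal reading patients can enter days after healing who are not PHN cases by the article's own description. The application of elimination criterion 1 changes with the reading. That part rests on the text alone and needs no assumption beyond taking a month as 30 days.

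The covariate offers a possible gain in precision, and its size cannot be derived from the documents. The 82% to 92% range depends on an assumed R² of 5% to 30%, a two-sided test and 57 analysed per group. The imbalance figures depend on an assumed share of recent cases and an assumed difference in their course. Neither set of figures is evidence that the trial is biased or underpowered.

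**What to change.** 1. Reconcile inclusion criterion 2 with the Introduction by stating the event from which the 30 days are counted, and apply the same wording when elimination criterion 1 is used. This is one sentence. If the clock starts at healing, a few screened patients may wait some weeks before they qualify (25 days in the example above).
2. Record pain duration at screening, which criterion 2 requires under either reading, or time since healing if that becomes the clock. Name it before unblinding as a covariate in the between-group comparisons of ZBPI and QST, in place of the repeated-measures ANOVA without covariates. Fix its form in advance, for example on a log scale, because with no upper limit a few very long durations could dominate a linear term. Say also how it enters if the skewed-data route to non-parametric tests is taken. The cost is one model term, with no added visits.
3. Stratifying the central randomisation by duration is optional. It would add one factor to the existing system and is not needed to resolve the point. If the full protocol or analysis plan already specifies a duration covariate, only item 1 remains.

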### Discontinuation Criteria

(1) Subjects have serious adverse reactions during the study and it is not appropriate to continue participating in the trial;(2) Subjects have serious complications or deteriorating conditions during the study and emergency measures are urgently needed;(3) Subjects ask to quit the trial halfway;(4) Subjects have poor compliance and cannot comply with the study protocol.

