### Elimination Criteria

(1) Subjects don't meet the inclusion criteria but they are included in the trial by mistake;(2) Subjects don't follow the prescribed treatment or have incomplete data that affects the efficacy evaluation and safety evaluation;(3) Subjects with poor compliance and withdraw from the study by themselves;(4) Subjects received adjunctive treatments other than the intervention of this trial.

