### Outcome Measures

#### Primary Outcome Measures

(1) Change in sensory perception measured by quantitative sensory testing (QST);QST is a psychophysical test method that investigates the functional state of the somatosensory system by means of calibrated stimuli and subjective perception thresholds (13). It is a valid and reliable test method that is often adopted in trials involving HZ or PHN (14, 15). QST will be performed in accordance with the protocol developed by the German ResearchNetwork on Neuropathic Pain (DFNS) that was described in details elsewhere (16) and in brief, multiple tests will be performed as supplied in Appendix 1.(2) Change in pain intensity measured by Zoster Brief Pain Inventory (ZBPI) instrumentZBPI is a herpes zoster specific questionnaire to quantify pain and discomfort in HZ and PHN patients. The validity and reliability of the ZBPI as an outcome measure for HZ or PHN has been proved (17), so it is frequently used in trials involving PHN patients (18, 19). The detailed questionnaire of ZBPI is supplied in Appendix 2.

Primary outcomes will be assessed before intervention, at 2, 4, 6 weeks after intervention and at the end of 8-week follow-up.

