### Safety Evaluation

The indicator of safety evaluation is the frequency of adverse events (AEs) arisen during the treatment course. For this trial, AEs related to acupuncture and EA mainly include unbearable pain, bleeding, haematoma, skin pigmentation, skin allergies, fainting/sweating/dizziness during acupuncture, or other uncomfortable symptoms. AEs related to medication mainly include gastrointestinal discomfort and drug allergies. AEs that occur throughout the study will be assessed and recorded and by the investigators. Investigators should also record the occurrence date, degree, duration, and treatment measures of AEs.

At occurrence of AEs, emergency measures will be taken in a timely manner. For serious AEs, the researchers should report to the principal investigator and ethics committee immediately, who will determine whether the participant should be withdrawn from the study.

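### The response to a serious adverse reaction is worded as leaving the trial rather than stopping study treatment, so later safety and outcome data may be lost for harm-related reasons

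*Protocol article*

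**What the plan says.** The Discontinuation Criteria section has four items. Item 1 is "Subjects have serious adverse reactions during the study and it is not appropriate to continue participating in the trial". Item 2 concerns serious complications or deterioration that call for emergency measures. Item 3 is "Subjects ask to quit the trial halfway" and item 4 is "Subjects have poor compliance and cannot comply with the study protocol". Items 1 and 3 refer to leaving the trial. Items 2 and 4 give a trigger and no consequence.

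The Safety Evaluation section sends serious adverse events to the principal investigator and ethics committee, "who will determine whether the participant should be withdrawn from the study". It also says "AEs that occur throughout the study will be assessed and recorded" and "Investigators should also record the occurrence date, degree, duration, and treatment measures of AEs".

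Item 2 of the Elimination Criteria covers subjects who do not "follow the prescribed treatment or have incomplete data that affects the efficacy evaluation and safety evaluation". Item 4 of that list covers subjects who received treatment additional to the trial intervention.

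On timing, "Primary outcomes will be assessed before intervention, at 2, 4, 6 weeks after intervention and at the end of 8-week follow-up". Table 1 places the safety assessment at weeks 2, 4, 6 and 14 and the recurrence assessment at week 14 only. Under Quality Control, dropouts and withdrawals are to be documented; continued visits for these patients are not mentioned.

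**The concern.** Stopping a treatment and leaving a trial are different events. A patient who cannot tolerate more electroacupuncture or gabapentin can still be asked about pain and adverse events at week 6 and week 14. The two places where this article states what follows serious harm both describe the second event and do not offer the first.

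Read as written, an exit decided for harm ends follow-up for a reason tied to what the trial measures. The triggering event has been seen and counts. What may be lost is everything after it: the duration of an event still ongoing at exit, any later events, both primary outcomes (QST and ZBPI) and the recurrence assessment. Data lost for this reason may be informative about safety and pain.

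The Elimination Criteria add a second route to the same loss. A patient who stops treatment because of harm but attends every visit has still departed from the prescribed treatment, which is a listed ground for elimination. If emergency or rescue treatment was needed, item 4 of that list could apply as well.

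**Working it through.** **1. Where the text names trial exit.**
- Discontinuation item 1: yes. It applies only if continued participation is judged inappropriate.
- Safety Evaluation, serious adverse events: yes, as a question to be decided for each patient.
- Discontinuation item 3: yes, at the patient's own request. This is not challenged.
- Discontinuation items 2 and 4: no. They sit in the same list, but the consequence is not stated, and item 4 concerns compliance rather than harm.

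The point therefore rests on item 1 and the Safety Evaluation section.

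**2. What one exit can cost.** The input is Table 1. After baseline there are four visits: weeks 2, 4, 6 and 14. Seven rows recur at each visit: QST, ZBPI, analgesic dosage, SF-36, HADS, PSQI and safety. Recurrence adds one assessment at week 14. The total is 7 × 4 + 1 = 29. If visits stop at exit, the loss is 7 × (visits remaining) + 1 overall, 1 × (visits remaining) for safety and 2 × (visits remaining) for QST plus ZBPI.

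| Exit | Safety lost, of 4 | QST and ZBPI lost, of 8 | All lost, of 29 |
|---|---|---|---|
| before week 2 | 4 | 8 | 7 × 4 + 1 = 29 (100%) |
| weeks 2–4 | 3 | 6 | 7 × 3 + 1 = 22 (76%) |
| weeks 4–6 | 2 | 4 | 7 × 2 + 1 = 15 (52%) |
| weeks 6–14 | 1 | 2 | 7 × 1 + 1 = 8 (28%) |

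The first three rows include the week 6 ZBPI, on which the Sample Size Estimation section rests. All four rows include the recurrence assessment.

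**3. Set against the planned numbers.** The section asks for 57 per group, assumes 15% dropout and enrols 66. That figure reproduces as 57 × 1.15 = 65.55, rounded up to 66. (Dividing instead, 57 / 0.85 = 67.06, rounds up to 68.) The margin is 66 − 57 = 9 per arm, for all causes of loss. One exit before week 6 is 1/66 = 1.5% of an arm and uses one of those nine. The nine is not an estimate of harm-related exits.

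**4. Power, for scale only.** The pilot effect and its SD are not given. Assuming a two-sided 5% test and a normal approximation for two means, 57 per group with 80% power implies a standardised difference of about 0.525. At that value, power is about 85% with all 66 per arm, 82% at 10% loss, 79% at 15% and 77% at 20%. Dropout at the planned rate is thus largely allowed for. The issue is which patients go missing more than how many.

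**5. Whether other text secures the data.** The Safety Evaluation section asks for adverse events across the study and for their duration. That may imply following an event to its end, but it is tied to a study the patient would have left. Quality Control requires withdrawals to be documented, which is not the same as continuing to assess those patients.

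**The case against.** The strongest reply is that this is a condensed article. It lists criteria and gives no procedure for what happens after discontinuation, which a full protocol would normally contain. Nothing here says visits stop. The wording is conditional in both places, so a patient with a serious event may remain. There are also safeguards: immediate reporting of serious events, recording of degree and duration, a data safety monitoring committee and documented withdrawals. The sample size already allows for dropout, and no bias is demonstrated.

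Much of this stands. Loss of visits is an inference, and the fuller protocol could add follow-up. It does not remove the point, because the consequence printed here is trial exit and the elimination grounds are printed too. The safeguards capture the triggering event; they do not secure what comes after it.

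A reader might infer more than the document supports:
- **Every serious reaction ends participation.** Both statements leave this to judgement.
- **All four discontinuation items are trial exits.** Items 2 and 4 do not say so.
- **The results would be biased towards one arm.** The electroacupuncture arm has 30 sessions and its own list of expected events, so exits could differ between arms, but the document gives no rate or direction. Whether the lost data would be missing at random given earlier visits cannot be judged either.

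**Conclusion.** The point holds in limited form, as a cheap improvement. Discontinuation item 1 and the Safety Evaluation section word the response to serious harm as leaving the trial or study, and Elimination item 2 can then remove a patient for being off treatment or incomplete. Following these rules can drop patients from follow-up and analysis for harm-related reasons.

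The size per patient is 8 to 29 of 29 scheduled assessments, on the assumption that visits stop at exit. The number of such patients, the direction of any effect and any difference between arms are unknown and are not estimated here. Discontinuation items 2 and 4 need only a clarification. How elimination acts on each analysis is not described in the article, so its effect there is also conditional.

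**What to change.** **Discontinuation Criteria.** Reword item 1 so that the consequence is withdrawal from study treatment. Clarify that items 2 and 4 also stop treatment only. Keep the Table 1 safety and outcome visits through week 14 unless the patient withdraws consent to follow-up or cannot attend. Leave item 3 as it is.

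**Safety Evaluation.** Make the decision after a serious adverse event one about withdrawal from study treatment. Follow events ongoing when treatment stops until they resolve or stabilise.

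**Elimination Criteria.** State that stopping treatment for harm or deterioration, or receiving emergency or rescue treatment as a result, does not by itself trigger elimination under item 2 or item 4. Without the reference to item 4, the same patients could still be removed for the rescue treatment they needed.

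**Cost.** Wording in three sections. The visits are already scheduled, and Quality Control makes outcome measurements free to participants. The sample size, alpha and clinical grounds for stopping do not change. Some patients will decline visits; a telephone check can replace the safety visit but not QST. The week 6 comparison will include some patients who are off treatment, which may slightly dilute the difference between arms.
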